### Intervention

The *IBIS-Survivorship* model of care is a multifaceted intervention that includes a prespecified shared care pathway between oncology specialists and GPs following completion of primary cancer treatment. table 1 outlines the three key activities that comprise the intervention and figure 2 outlines the expected *IBIS-Survivorship* shared care pathway. Activity 1: within 6 weeks to 10 weeks after the completion of active treatment, a 30–60 min consultation between the participant and the BCN is conducted to discuss treatment, provide education and to develop a Survivorship Care Plan (SCP). The SCP will include goal setting of up to three SMART (specific, measurable, achievable, realistic and timely) goals that are developed in partnership between the participant and the BCN, using motivational interviewing and self-efficacy techniques. The initial SCP will be sent to the GP and the participant within 3 days of this consultation. Activity 2: within 4 weeks of the nurse-led consultation, a 20–30 min case conference between the BCN and the participant’s nominated GP is completed to discuss the shared follow-up care schedule, discuss the SCP and negotiate the GP’s role in facilitating the SCP goals. The GP may propose changes or express if they are not willing to take part in specific care activities outlined in the SCP. If a formal case conference is not achievable, a short phone call between the BCN and GP will occur, and if no contact with the GP can be made, a copy of the SCP will be sent to the GP practice records. Activity 3: the participant attends a GP appointment to discuss the SCP, and the shared care follow-up schedule commences consisting of 6 monthly appointments with the oncology specialist team and annual appointments with the GP for up to 5 years post-diagnosis. The GP will be provided with direct telephone access to the BCN in case of concerns or escalation for acute care review. At 5 years, the patient will be discharged to the care of the GP.

**Table 1 T1:** Active ingredients of the IBIS-Survivorship intervention model

Active ingredient	Personnel involved	Specific activities	Note
BCN-led consultation providing treatment summary and survivorship care planning (SCP; 30–60 min)	BCN, participant	Treatment summary, co-draft SCP, collaborative planning for health goals, post-treatment education, motivational interviewing and assessment of self-efficacy.	The completed treatment summary and draft SCP will be sent to GP within 1 week after this BCN-led clinic. The BCN will organise the case conferencing with the GP.
Case conferencing with GP (duration variable pending GP availability and need)	BCN, GP	BCN to present the treatment summary and SCP. BCN to negotiate follow-up responsibilities with the GP and respond to GP queries.	Draft SCP will be sent to the GP and the participant. A final copy will be added to the medical record.
Standardised shared follow-up care between oncology specialists and GPs (duration variable pending need)	Oncology specialist(s)*, GP, patient	The oncology specialist(s) to review the patient, order and review the mammogram and undertake a full physical examination every 12 months.The GP to review the patient at least every 12 months to carry out SCP-specific care activities†	The GP and the participant have the direct telephone number of the relevant BCN for advice or to escalate interventions to return to acute care for review.

* Oncology specialists can refer to surgeons, medical oncologists and radiation oncologists.

† Activities may include, but are not limited to, general health and comorbidity management, psychosocial screening and health management, management of cancer treatment toxicities and cancer-related symptoms; chronic disease management planning and subsequent allied health referrals.

BCN, Breast Cancer Nurse; GP, General Practitioner; SCP, Survivorship Care Plan.

### Control arm

Participants who are enrolled in the control arm will receive usual care or the support they usually receive from their healthcare teams. The current follow-up arrangement in all participating clusters is a specialist-led model as determined by the individual treating surgeons, medical oncologists or radiation oncologists. Usual care may differ at each site. All participants will be provided with a written survivorship booklet ‘Living Well After Cancer’ published by Cancer Council Australia^38^ regardless of arm assignment.

### Outcomes

#### Effectiveness outcomes

##### Primary endpoint

HRQoL as measured by the Functional Assessment of Cancer Therapy - Breast Cancer (FACT-B)^39^ at 12 months post enrolment is the primary outcome measure. This validated and reliable tool is well accepted for use in cancer survivors undergoing and beyond treatment^40^ and captures key domains of QoL and key symptoms that are relevant to the study population and sensitive to changes over time.

##### Secondary endpoints

The secondary endpoints include a range of quantitative patient-reported outcomes at 6 months and 12 months post-enrolment (T2, T3) outlined in table 2. Furthermore, open-ended responses exploring participant satisfaction with the *IBIS-Survivorship* model will be collected through the T3 survey.

**Table 2 T2:** Measurement and data collection schedule

Setting	RE-AIM indicator	Collection method/ tools	Study period			
			T1	T2	T3	End of study
*Primary outcome*						
Patient	Effectiveness					
	Health-related quality of life (HRQoL)	Self-report: Functional Assessment of Cancer Therapy - Breast Cancer.^39^ This validated and reliable tool is well-used in cancer survivors undergoing *and* beyond treatment,^40^ and it captures key domains of HRQoL/key symptoms relevant to the study population.	✓	✓	✓	
*Secondary outcomes*						
Patient	Effectiveness					
	Patient experience of care	Self-report: Patient Assessment of Care for Chronic Conditions includes 20 items derived from the '5As' model (ask, advise, agree, assist and arrange), a patient-centred model of behavioural counselling that is congruent with the Chronic Care Model and has been frequently used to enhance self-management support and linkages to community resources.		✓	✓	
	Symptom burden and distress	Self-report: Memorial Symptom Assessment Scale (MSAS)^48^ including MSAS-GDI (Global Distress Index), MSAS-PHYS (physical symptom distress) and MSAS-PSYCH (psychological symptom distress) subscales. This tool is valid and reliable in measuring symptom prevalence, characteristics, frequency, severity and distress in patients with cancer.^48^	✓	✓	✓	
	Cancer-related fatigue	Self-report: Brief Fatigue Inventory. This tool is reliable in assessing the severity of fatigue and the impact of fatigue on daily functioning in patients with cancer.	✓	✓	✓	
	Comorbidity burden	Self-report: A suite of questions from the Self-Administered Comorbidity Questionnaire,^49^ Charleston Comorbidity Index and Medicare Comorbidity list.	✓		✓	
	Diet and physical activity behaviour	Self-report: Short dietary questions related to fruit and veg intake^50^; Active Australia Survey^51^ and single item from the International Physical Activity Questionnaire short-form.^52^	✓	✓	✓	
	Financial Toxicity (FT)	Self-reports: 11-item COmprehensive Score for financial Toxicity-Functional Assessment of Chronic Illness Therapy tool.^53^ This tool is valid and reliable in measuring FT in patients with cancer.^54^	✓	✓	✓	
	Satisfaction of care	0–10 numerical analogue scale (with 10 being the most satisfied) supplemented with short qualitative interviews.			✓	✓
	Unplanned hospital admissions	Self-report (verified with hospital records)		✓	✓	✓
	Adherence to annual mammogram, physical breast exam and endocrine therapy	Hospital records			✓	✓
Cancer Centre	Reach and representativeness					
	Demographics	Self-report: age, gender, ethnicity, education, living arrangements, marital status, children (including ages) and employment	✓			
	Medical history	Hospital records and self-report: Previous cancer diagnoses and treatments	✓			
	Clinical characteristics	Hospital records and self-report: Breast cancer diagnosis and treatment protocols received	✓			
	Adoption and maintenance (sustainability)					
	% GPs explicit engagement in case conference	Records in database				✓
	Implementation					
	Completion (Y/N) and duration (min) of BCN-led consultation	BCN records, completion of the BCN-led consultation checklist and RN records in database				✓
	Completion (Y/N) and duration (min) of Case Conferencing with GP	BCN records, completion of the GP Case-conference checklist.				✓
	Completed survivorship care plan/components (Y/N)	BCN records, Survivorship Care Plans				✓
	Completed Chronic Disease Management plan (Y/N)	MBS (by GP)				✓
	No. and timing of GP visits and specialist visits	MBS and patient self-report (verified with hospital records)				✓
	Health provider satisfaction	Semistructured interviews				✓
	Economic appraisal					
	Cost-effectiveness	Self-report: The EQ-5D-5L is a standardised measure of health status developed by the EuroQol Group to provide a simple, generic measure of health for clinical and economic appraisal.^55^ The EQ-5D 5 L is a valid, reliable and responsive instrument with published Australian value sets for calculating quality-adjusted life years	✓	✓	✓	

T1=baseline/enrolment; T2=6 months post enrolment; T3=12 months post enrolment.

BCN, Breast Cancer Nurse; CDM, Chronic Disease Management plan; EQ 5D-5L, EuroQol 5 Dimensions 5 Levels; GP, primary care physician; MBS, Medicare Benefits Scheme; RE-AIM, Reach, Effectiveness, Adoption, Implementation and Maintenance.

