## Methods and analysis

This study protocol (V.2.4) was written in accordance with the Standard Protocol Items: Recommendations for Interventional Trials guidelines^24^ (see online supplemental material A).

The proposed study will use a SW-CRT design to deliver the *IBIS-Survivorship* model sequentially in six acute care cancer centres across metropolitan and rural Australia. *IBIS-Survivorship* is a multicentre, prospective, pragmatic type II hybrid effectiveness-implementation trial of a nurse-enabled shared care model. Our primary hypothesis is that participants receiving the *IBIS-Survivorship* intervention will have a significantly better breast cancer-specific health-related quality of life (HRQoL) at 12 months post enrolment, compared with those receiving usual care. Secondary hypotheses are that participants receiving *IBIS-Survivorship* will have higher satisfaction with care; higher uptake of healthy lifestyle behaviours and equivalent adherence to annual mammography, annual physical examination and endocrine therapy at 12 months post enrolment. It is, however, acknowledged that the collection of these adherence outcomes for the longer term will require additional resources to follow patients. We also hypothesise that *IBIS-Survivorship* will be more cost-effective compared with usual care. Implementation and process outcomes will be assessed using the Reach Effectiveness Adoption Implementation Maintenance (RE-AIM) Framework.^25^

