### Participant screening and consent

Research nurses will carry out initial screening to identify potential participants. Potential participants will then be reviewed according to the eligibility criteria by a member of the treating team, and if suitable, asked if they agree to be approached by a research nurse for consent to the study. These potential participants will be provided with a brochure giving detailed information about the study objectives and a Participant Information and Consent Form (PICF) providing details of the study assessments and procedures (online supplemental material B). Participants will be given up to 2 weeks to consider their participation. Participants will provide written informed consent to be enrolled into the trial. All participants will be asked to consent to allow the study team access to their medical record, and a separate written consent form will be used to indicate the participant’s willingness to allow for access to Australian Medical Benefits Schedule and Pharmaceutical Benefits Scheme (PBS) data through Services Australia.

Once a participant consents, this will be recorded in a REDcap^27 28^ database and they will be assigned a unique study ID number. Participants will be automatically invited to complete a baseline survey (T1) on enrolment. This provides sociodemographic information, medical/health history and baseline measures for patient-reported outcomes. If they do not complete this survey within 10 weeks of completion of adjuvant cancer therapies or surgery, the participant will be withdrawn from the study.

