### Cost-effectiveness

A cost-effectiveness analysis will be undertaken to assess whether the *IBIS-Survivorship* model provides value for money compared with usual care. Additionally, costs of the intervention and health service use will be aggregated and patient benefits assessed. Intervention costs will be monitored by the study coordinator. Health service use will be captured on linked national administrative health datasets. Medicare Benefits Scheme and PBS data will be obtained from participants who provide consent to access this data and will include relevant claims details (ie, date of service, Medicare item number and description), cost details (ie, provider charge, scheduled fee, benefit paid, out of pocket expenses and billing type), service provider and referrer details (ie, provider specialty and item category). Unique study codes will be assigned to participants to link records uniquely and anonymously for analysis and ensure confidentiality is maintained. Strict data typographical verification protocols and consistency check protocols will be employed. Similarities and differences in datasets will be identified before results are aggregated.

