#### Clinical data

Information about the participant’s cancer (histology, grade and stage of disease at diagnosis), date of diagnosis and treatment (surgery, chemotherapy and radiotherapy doses and dates) is obtained from medical records at T1 and entered into the REDCap database. Information will be obtained from health service medical records relating to hospital admissions and follow-up appointments including physical breast exam, mammography and endocrine therapy adherence occurring within the first 12 months post enrolment.

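### Endocrine-therapy adherence rests on hospital records alone despite an equivalence hypothesis; the PBS data already being obtained should be added as a second source

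*Protocol article*

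**What the plan says.** The secondary hypotheses in the Protocol article (Methods and analysis) include "equivalent adherence to annual mammography, annual physical examination and endocrine therapy at 12 months post enrolment".

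Table 2 (Secondary endpoints) has one row for "Adherence to annual mammogram, physical breast exam and endocrine therapy". Its collection method is hospital records and nothing else. The Clinical data section says the same: "Information will be obtained from health service medical records relating to hospital admissions and follow-up appointments", covering breast examination, "mammography and endocrine therapy adherence occurring within the first 12 months post enrolment". No claims, GP or self-report source is named for this outcome in either place.

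The Cost-effectiveness section states that "Medicare Benefits Scheme and PBS data will be obtained from participants who provide consent to access this data". Participant screening and consent adds that "a separate written consent form will be used to indicate" willingness to allow this access. The article does not link PBS data to adherence.

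**The concern.** The outcome asks whether a medicine is being taken over a year. Its only source is a record of hospital contacts, which captures what was prescribed or discussed at a visit. Someone who stops between visits, or never fills a prescription, can remain on treatment as far as the chart shows.

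This matters more under a hypothesis of equivalence than under one of difference. Insensitive measurement usually costs a trial the ability to show a benefit. Here it makes the hoped-for conclusion easier to reach, because a real loss of adherence is diluted.

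There is a second risk. Control follow-up is specialist-led. The intervention adds a nurse consultation, a care plan filed in the medical record, a GP case conference and scheduled GP review. What reaches the hospital chart may therefore differ by arm even when true adherence does not.

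**Working it through.** The plan states no adherence, capture or PBS consent rate, so there is no figure to reproduce. The check sets the passages side by side and then shows how the two mechanisms act under labelled assumptions.

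**1. Sources named for comparable outcomes (Table 2).** Among the patient-level effectiveness outcomes:
- Unplanned admissions: self-report, verified with hospital records.
- Adherence: hospital records only, the only row in that block resting on them alone.

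Elsewhere in Table 2, GP and specialist visit counts come from MBS claims and self-report, verified with hospital records. The plan thus already combines claims with hospital records for another measure.

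**2. Which components are exposed.** Table 1 leaves ordering and review of the mammogram, and the annual physical examination, with the oncology specialist in the intervention arm. These should appear in hospital records. Endocrine therapy is what remains.

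**3. Missed discontinuation, equal in both arms.** Suppose a chart that is silent about stopping is read as continuing, and charts detect a fraction d of true non-adherence, with no false detections.

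- Recorded difference = d × true difference.
- Assumed true non-adherence 20% v 30%, d = 0.5: 0.5 × 20% = 10% and 0.5 × 30% = 15%.
- A true gap of 10 points is recorded as 5. As d runs from 1 to 0, the recorded gap falls from 10 points to none.

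This needs no assumption about which arm is better recorded.

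**4. Recording that differs by arm.** Suppose instead that adherence counts only when documented. Recorded adherence = true adherence × capture. Assume true adherence is the same in both arms, at 80% (range 70% to 90%).

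| Capture, control | Capture, intervention | Recorded at 80% | Spurious difference at 80% (range for 70–90%) |
|---|---|---|---|
| 95% | 95% | 76% v 76% | 0 |
| 95% | 90% | 76% v 72% | −4 points (−3.5 to −4.5) |
| 95% | 85% | 76% v 68% | −8 points (−7 to −9) |
| 90% | 95% | 72% v 76% | +4 points (+3.5 to +4.5) |

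The sign follows the assumed capture rates, and the documents give no basis for choosing among the rows. Under the reading in step 3 the sign would also turn round, because better recording in one arm would uncover more stopping there.

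**5. Whether a second source is within reach.** PBS access is covered by a separate written form described with enrolment consent. Under Randomisation and blinding, participants learn their arm at the first clinical appointment after enrolment. That limits arm-related selection into PBS consent but does not exclude it. Data collection was expected to finish in November 2025, and claims need no further patient contact.

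**The case against.** A reader might infer that follow-up moves to GPs, so that adherence will be under-recorded in the intervention arm. The documents do not support this:

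- The Intervention section keeps "6 monthly appointments with the oncology specialist team and annual appointments with the GP for up to 5 years post-diagnosis", and discharge to the GP comes only at 5 years. Table 1 has specialist review every 12 months. The two frequencies should be reconciled, but under either a specialist review falls due within the 12-month window.
- Table 1 says "The GP to review the patient at least every 12 months to carry out SCP-specific care activities". Nothing there or in its footnote says that endocrine prescribing passes to the GP.
- The nurse consultation, treatment summary and filed care plan could improve hospital recording in the intervention arm. Usual care may differ by site, and its visit frequency is not stated.

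Nor does the concern extend to mammogram and physical examination, or make adherence a named safety indicator: the abstract uses that term generally, and Table 2 places adherence under effectiveness.

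Against the remedy, PBS data cover a separately consented subset of unknown size. Recruitment closed in November 2023, so consent taken at enrolment cannot be widened. The claims fields listed do not mention quantity or days supplied. These points stand, and they rule out replacing hospital records with PBS.

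Finally, the article is condensed, and an adherence definition may sit in the full protocol or SAP. That excuses a missing definition. It does not remove the point that two places in the article specify a single source.

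**Conclusion.** The point holds for endocrine therapy. Hospital records are fixed as the only source for an outcome carrying an equivalence hypothesis, although data closer to supply and continuation are already requested. Charts can miss discontinuation and so draw a real difference towards equivalence. Recording may also differ between arms, in a direction that the documents do not settle.

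The size cannot be computed from the documents. The halving of a 10-point gap, and the spurious differences of −9 to +4.5 points, rest wholly on assumed detection and capture rates; equal capture gives no spurious difference. The outcome is secondary and the primary FACT-B analysis is unaffected. The change is still worth making, because the present source favours the hypothesised result and the supplement is cheap.

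**What to change.** In Table 2 and in the Clinical data section, name PBS dispensing over the first 12 months after enrolment as a second source for endocrine-therapy adherence, for participants prescribed it who gave claims consent. Define one derived variable, for example continued supply or discontinuation. Confirm first that the consent covers this use and that the extract holds the fields needed; a measure based on days covered would need quantity supplied.

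Keep the hospital-record result for all participants and report the two side by side. Give PBS consent rates by arm and the agreement between sources among those who have both. Leave the source for mammogram and physical examination as it is.

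The cost is a change of wording in two places, one derived variable and one additional analysis from data already requested. The downside is that the claims-based result covers only those who gave the separate consent, so it supplements the hospital-record result and does not replace it.

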### Implementation outcomes

The implementation of *IBIS-Survivorship* will be assessed according to the five components of the RE-AIM Framework,^25^ with outcomes and data collection methods summarised in table 2. Relevant outcomes include representativeness of the patient population according to demographic and clinical characteristics (*reach*), proportion of GPs that explicitly engage in the intervention (*adoption*), attendance rates and process outcomes of the BCN consultation and GP case conference such as how long it took to run each session and the percentage of planned components within each that were implemented (*implementation*) and key factors that facilitate or hinder the sustainability of the *IBIS-Survivorship* model (*maintenance*).

### Cost-effectiveness

A cost-effectiveness analysis will be undertaken to assess whether the *IBIS-Survivorship* model provides value for money compared with usual care. Additionally, costs of the intervention and health service use will be aggregated and patient benefits assessed. Intervention costs will be monitored by the study coordinator. Health service use will be captured on linked national administrative health datasets. Medicare Benefits Scheme and PBS data will be obtained from participants who provide consent to access this data and will include relevant claims details (ie, date of service, Medicare item number and description), cost details (ie, provider charge, scheduled fee, benefit paid, out of pocket expenses and billing type), service provider and referrer details (ie, provider specialty and item category). Unique study codes will be assigned to participants to link records uniquely and anonymously for analysis and ensure confidentiality is maintained. Strict data typographical verification protocols and consistency check protocols will be employed. Similarities and differences in datasets will be identified before results are aggregated.

